### Protocol deviations

Any deviation from the agreed protocol will be recorded. Any amendments that may be required once the trial has been initiated will be submitted for ethics committee approval prior to implementation.

### Interim analyses and Data Monitoring Committee (DMC)

The first monitoring analysis of the primary end will be performed once 50 patients have completed their 1 week post-operative assessment. The data will be supplied to an independent data monitoring committee (DMC), which will be asked to give advice on whether the accumulated data from this trial, justifies its continuation. The independent DMC will comprise a statistician, an orthopaedic surgeon, and a clinical researcher.

The decision to discontinue will only be made if the results are likely to be convincing to a broad range of clinicians including participants in the trial and the general clinical community. A nominal significance level for stopping the trial will be p <= 0.02 [15].

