## Statistical considerations

### Sample size

In a group of 86 patients undergoing total knee arthroplasty the mean 1 year post-operative Knee Society Score was 172.2 with a standard deviation of 20 and a range of 98–200 [14]. To detect a 5% increase in the post-operative Knee Society Score in the sub-vastus group compared to the medial parapatellar group with a two sided significance level of 5% and a power of 90% a sample size of 105 patients would be required in each group. An additional 10% will be recruited to each group to allow for any patients lost to follow-up, giving a total sample size of 231.

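### The 0.02 stopping level and the unadjusted 5% design level do not fit together: either overall type I error can exceed 5%, or power falls below plan

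*Protocol article*

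**What the plan says.** The section on interim analyses and the DMC states: "The first monitoring analysis of the primary end will be performed once 50 patients" have reached their 1-week assessment. The data then go to an independent committee, which advises on whether the trial should continue. The numerical criterion is: "A nominal significance level for stopping the trial will be p <= 0.02 [15". The same section adds that the trial stops only if the results would persuade clinicians generally. It does not give the number of looks that follow the first, or the level for the final test.

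The Sample size section calculates "with a two sided significance level of 5% and a power of 90" per cent, from these inputs: "the mean 1 year post-operative Knee Society Score was 172.2 with a standard deviation of 20", and a target of a 5% increase. It concludes that "a sample size of 105 patients would be required in each group". The only inflation is for loss to follow-up: "An additional 10% will be recruited to each group to allow for any patients lost to follow-up, giving a total sample size of 231". Nothing is added for interim testing.

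The Data analysis section gives no significance level. The Assessment of outcome section places the primary outcome at 52 weeks. The 0.02 and the 5% are therefore the only two significance levels in the document, and no sentence connects them.

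**The concern.** A constant nominal level near 0.02 can control the overall error, but only if the number of analyses is fixed in advance and the final analysis uses a level that goes with it. Here the word first implies that more looks may follow, none is counted, and the trial is sized as if a single test at 5% would be made.

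Two stated properties are at stake. If the final test uses the 5% of the sample size calculation, early stopping at 0.02 is extra opportunity for a false positive. If the final test uses 0.02, the sample size was computed at the wrong level.

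The timing adds weight. The first look comes at 50/231, about 22% of the planned patients, where a difference large enough to cross 0.02 is likely to be an overestimate.

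**Working it through.** **Inputs from the Sample size section.** Mean 172.2, SD 20, difference 0.05 × 172.2 = 8.61, two-sided 5%, power 90%, 105 per group, total 231. **From the interim section.** First look at 50 patients, stopping at p ≤ 0.02. **Assumptions.** 0.02 is two-sided, allocation is equal, and the trial stops at every crossing.

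**Step 1: the plan's own figure.** n per group = 2 × (1.960 + 1.282)² × 20² / 8.61² = 113.4, so 114, not 105. A difference rounded to 9 points gives 104 (105 with the t distribution), which may be the source. The total does reproduce: 105 × 1.1 × 2 = 231. This discrepancy is a separate matter, but it affects the power comparison in step 4.

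**Step 2: one look, final test at 5%.** Overall error = 1 − P(|Z₁| < 2.326 and |Z₂| < 1.960).
- If the look and the final test measure the same endpoint, the correlation is √(50/231) = 0.465 and the error is 6.6% (6.5% with 50/210).
- If 1-week scores are unrelated to 52-week scores, the correlation is 0 and the error is 1 − 0.98 × 0.95 = 6.9%.
- Intermediate correlations lie between these two values.

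**Step 3: more looks.** The protocol gives no schedule, so a look every 50 patients out of 231 is assumed for illustration. Half correlation means that the correlation of each interim with the final test is multiplied by 0.5.

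| Interim looks | Final 5%, same endpoint | Final 5%, half correlation | Final 0.02, same endpoint | Final 0.02, half correlation |
|---|---|---|---|---|
| 1 | 6.6% | 6.8% | 3.8% | 3.9% |
| 2 | 7.5% | 8.1% | 4.9% | 5.3% |
| 3 | 7.9% | 9.0% | 5.6% | 6.3% |
| 4 | 8.1% | 9.7% | 6.1% | 7.1% |

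A constant 0.02 on one endpoint therefore holds 5% with up to two interims, but not with three.

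**Step 4: power of the final test, 105 per group.** The standard error is 20 × √(2/105) = 2.760, and 8.61 / 2.760 = 3.119.
- Level 0.05: 3.119 − 1.960 = 1.159, power 87.7%.
- Level 0.033: 3.119 − 2.132 = 0.987, power about 84%.
- Level 0.031: 3.119 − 2.157 = 0.962, power about 83%.
- Level 0.02: 3.119 − 2.326 = 0.793, power about 79%.

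**Step 5: final level that restores 5% after one look at 0.02.** Solving the step 2 formula for the final level gives about 0.033 on the same endpoint and about 0.031 with zero correlation.

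**Step 6: what crossing 0.02 at the first look requires.** With 25 per group and SD 20 (assumed; no 1-week SD is given), the observed difference must be 2.326 × 20 × √(2/25) = 13.2 points, about 1.5 times the 8.61-point target.

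**The case against.** The strongest reply is that the document never says the final test stays at 5%. That figure is a sample size input. A nominal level supported by a citation could well be a constant level for all analyses, and with one or two interims on the same endpoint that keeps the overall error under 5%. This stands. A reader might infer that the trial's error rate is definitely above 5%, but the text supports only an either/or.

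Second, the rule is not automatic: the committee advises, and the results must also persuade clinicians. This stands too, so for a given schedule the error figures are upper bounds. It does not remove the problem, because 0.02 is the only numerical criterion and the further condition is not quantified.

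Third, a reader might take 7.5–8.1% as the trial's error rate. Those figures rest on an assumed look every 50 patients. Only the one-look range uses a look that the text describes.

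Fourth, a reader might charge the whole gap between 79% and 90% power to the stopping rule. Part of it is the separate sample size discrepancy: 105 per group gives only about 88% at 5%. The share due to the level is about 9 points.

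Fifth, the number of looks and the final level could stand in an analysis plan or committee charter. Their absence alone would be no finding. But the article does state a stopping level and a design level, and the sample size as stated allows for no interim testing.

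**Conclusion.** The point holds as a mismatch between two stated levels, not as proof that the error rate is inflated. With a 5% final test, the one described look takes overall type I error to about 6.6–6.9%, an excess of under 2 percentage points and an upper bound. Further looks would add to it. With 0.02 throughout, error is held for up to two interims on the same endpoint, but the final test has about 79% power instead of about 88% on the same inputs, and the stated 90% is not met. An intermediate final level of 0.031–0.033 after exactly one look keeps 5% overall at a cost of about 4 points of power. None of these readings delivers both the 5% and the 90% that the Sample size section states. The conclusion assumes a two-sided 0.02, equal allocation and SD 20. It is worth correcting because the rule governs both early stopping and the error rate of the primary comparison.

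**What to change.** State the number of looks, the interim level and the final level together.

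The simplest change is a stringent interim efficacy level, such as Haybittle–Peto p < 0.001. With looks every 50 patients on the same endpoint, a 5% final test then gives about 5.1% overall for one to four looks (about 5.3% at most, for four looks uncorrelated with the final test). The sample size level can stay as written. The cost is a few words in the protocol and the committee's charter, and a lower chance of stopping early.

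If 0.02 is kept, limit it to exactly one look at 50 patients and set the final level at about 0.033 if that look tests the same endpoint as the final analysis, or nearer 0.031 if it tests 1-week scores only weakly related to it. Restate power as about 83–84% for 8.61 points with 105 per group. Restoring 90% would take about 126–128 per group before allowance for loss to follow-up, against 114 at 5%.

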## Ethical considerations

This study has obtained ethical approval from the North Staffordshire Local Research Ethics Committee and Scientific Merit Committee.

## Informed consent

All eligible patients who agree to take part will sign an informed consent form. They will confirm that they have been given the information they require and that the study has been explained to them. Once a patient has consented to enter the trial, their GPs will be informed of their patients' involvement in the study.

## Confidentiality

Only the trial organisers/administrators will have access to patients' notes and questionnaires. All recorded information will be stored separately from patient names and addresses.

## Trial organisational structure

### Trial co-ordination

The day to day management of the trial will be co-ordinated from the local Musculoskeletal Research Department. The co-ordinating centre will be responsible for:

a) Processing and analysis of the trial data

b) Monitoring of data collection

c) Ensure confidentiality and security of all trial forms and data

d) Conduct data checking and cleaning

e) Interim and main analysis

### Clinical co-ordination

At the start of the trial representatives from the clinical centre along with the trial co-ordinator will visit surgeons with the aim of getting commitment to recruit patients into the study.

The Clinical Centre will:

(i) establish the trial locally with the assistance of the trial co-ordinator (for example getting agreement from colleagues, facilitating local research ethics committee approval, ensuring all clinical staff involved in the care of the patients are informed about the trial)

(ii) take responsibility for clinical aspects of the trial locally

(iii) be represented at SMAK arthroplasty trial meetings

A part-time study nurse will be based at the collaborating centre and will have responsibility for:

(i) keeping local staff informed about the trial and its progress

(ii) keeping regular contact with local surgeons and co-ordinating centre

(iii) identifying potential participants in advance of admission

(iv) taking responsibility for ensuring complete data collection

(v) getting arrangements in place for formal trial entry

(vi) facilitating progress of patients through the trial

In addition, a part time research physiotherapist will be based at the collaborating centre and will have responsibility for:

(i) assessment of functional capacity

(ii) liasing with research nurse to ensure timely assessment of outcome

## Discussion

There have been several trials comparing the subvastus and medial parapatellar approaches for patients undergoing primary total knee arthotomy. The major criticisms of the sub-vastus approach are poor and unpredicatable exposure, and difficulty with eversion of the patella [16,17]. Some studies have shown significant advantages in using the subvastus approach in relation to improved quadriceps strength [18], earlier straight leg raise, and lower analgesia use in the first week for the subvastus group [19,20]. These studies, however, only had small numbers and a short follow-up period, and not all patients were blinded to the approach used.

We present the rationale and design of a pragmatic randomised controlled trial comparing the sub-vastus approach to the standard medial parapatellar approach in terms of short and long term knee function for patients undergoing primary total knee replacement in which the patients are blinded to the approach used. The results of this trial will be beneficial for Orthopaedic Surgeons whom are under constant pressure to undertake techniques which aid quicker postoperative rehabilitation, and shorter hospital stay. The results of this trial will be published as soon as they become available.
